### Study site

This study will be conducted at the Kansas University Medical Center (KUMC) and will take advantage of the infrastructure of the UKanQuit smoking cessation program. KUMC is an ideal setting for the conduct of this study. KUMC boasts a research participant registry and an electronic medical record (EMR) with an I2B2 research interface that will facilitate recruitment of participants. The smokers seen at KUMC come from urban and rural locations throughout Kansas, but mostly from Kansas City, Missouri and Wyandotte County, Kansas. (Wyandotte County is a majority minority county that has the dubious distinction of being one of the most disadvantaged jurisdictions in Kansas.) Our study site will allow us to enroll a diverse population of smokers for this study, including African American and Latino smokers with COPD. The experienced researchers in the UKanQuit program have an outstanding track record for recruitment of high risk smokers into clinical studies, recently enrolling more than 1,000 hospitalized smokers into an NIH-funded study designed to enhance utilization of tobacco quit lines.

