#### **Study visits and data collection methods**

Trained research assistants will conduct assessments at baseline and 3, 6, and 12 months post-enrollment. Participants will receive a \$50 ClinCard for each assessment completed, which is similar to a prepaid credit card and can be used almost everywhere that credit cards are accepted. Compensation will not be contingent on smoking status. To help remove transportation barriers for participants without transportation who live within a reasonable distance from one of our site locations, we will offer to provide cab vouchers for participants to get to and from their appointments. In order to offset this cost, participants must be willing to have their payment for that visit reduced to \$30. To maximize retention, participants will be asked at the

baseline visit to provide contact information to facilitate follow-up: address, email, two telephone numbers if possible, and information for an alternate contact person. Reminder post cards and multiple calls will be used to maximize attendance at follow-up visits. To facilitate follow-up, staff will keep flexible hours providing opportunities for follow-up during evening and weekend hours. Follow-up will be conducted primarily at one of our two Clinical Research Units – both of which have easy parking within 100 feet of the door. To further facilitate follow-up, research assistants will also try to time follow-up assessments so that they can be coordinated with medical visits at KUMC.

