## Measures

**Outcome measures.** Our selection of outcomes was derived from scientific expert consensus and informed by input from our stakeholders and smokers with COPD. (Table 4) The primary outcome is biochemically verified 7-day point prevalence smoking abstinence defined as no cigarettes (not even a puff) for the previous 7 days at month 12. Biochemical validation will be based on expired CO, consistent with consensus statements from the Society for Research on Nicotine and Tobacco (SRNT). For those participants who have reported they have quit smoking and who are unable to be verified in this way, we will obtain verbal permission and contact information for a household member or other regular contact to provide proxy validation.

Secondary outcomes are 6 month sustained abstinence (biochemically verified), number of quit attempts, average CPD over the year of the study, and cumulative exposure to CO and NNAL. We will examine relapse rates 3 months after the conclusion of the study for participants who report they have quit smoking at the 12-month assessment. Clinical outcomes include both objective and subjective measures of respiratory function based on the measured FEV1 (as a percent of predicted) and the COPD Assessment Test.

We will also track both respiratory and cardiac clinical events. This will be done by self-report of intercurrent emergency department visits and hospitalizations at each follow-up visit. We will validate both the occurrence and the nature of these self-reported clinical events by blinded physician review of medical records.

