| Respiratory function                               | Simple spirometry will be performed at baseline and at the final follow-up visit. (baseline, Mo12)                                                                                                                                                                   |
| Respiratory symptoms                               | Respiratory symptoms will be measured using the COPD Assessment Test (baseline, Mo 3, 6 & 12)                                                                                                                                                                        |
| Respiratory-related hospitalizations and ED visits | Intercurrent hospitalizations and emergency department visits will be assessed at each follow-up visit. Patients will be asked to classify the event as related to their heart or breathing. These will be validated by blinded physician review of medical records. |
| Cardiac-related hospitalizations and ED visits     |                                                                                                                                                                                                                                                                      |

\*Primary outcome

self-report of CPD or they looked at nicotine metabolites (i.e. cotinine). Self-report of CPD is highly problematic, because even if smokers really do reduce the number of cigarettes they smoker, they tend to smoke those cigarettes more efficiently, and cotinine measurements are confounded by the use of therapeutic NRT. Our measures of CO and NNAL will allow us to have objective measure of actual smoke exposure. The NNAL is particularly relevant to our patients who would like to reduce exposure to carcinogens. NNAL (4-(methylnitrosamino)-1-(3)pyridyl-1-butanol) is a pulmonary carcinogen and metabolite of 4-(methylnitrosamino)-1-(3)pyridyl-1-butanone (NNK), a tobacco-specific nitrosamine related to the development of lung cancer. NNAL assessed in urine is highly correlated with smoke-related tobacco exposure.

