### Analytical Plan.

**Sample Size and Power Calculations.** Our sample size was based on our primary outcome, point-prevalence abstinence at Month 12, using an intent-to-treat approach. Based on prior studies using precessation NRT, we estimate a 2-fold increase in cessation outcomes in the LT-NRT group compared to the SSC group. Given our recruitment of patients at all levels of readiness to quit, we estimate a 12 month cessation rate of 10%. With 199 participants, in each arm, we will have an 80% power to detect a 2-fold difference or greater with a Type I error rate of 5%. This sample size will provide comparable power for looking at 6 month sustained cessation. For the CO measured longitudinally at four time points, we have 80% power to detect a mean difference of 2.24 ppm. Likewise, for NNAL, we have 80% power to detect a mean difference of 0.41 pmol/mg creatinine or more between the two groups.

**Specific Aim 1: Compare the benefits of traditional smoking cessation (SSC) versus long-term guided maintenance therapy (LT-NRT) with NRT.** The chi-square test will be used to compare the verified 7-day point prevalence abstinence at Month 12 between the two groups. If there is imbalance between treatment groups at baseline, we will switch to logistic regression for our primary analysis. We will use similar methods to test for group differences for dichotomous secondary outcomes including sustained abstinence and proportion with 1 or more ED visits or hospitalizations. To test for differences in change in respiratory symptoms and FEV1 from baseline measured at 3, 6, and 12 months, we will use standard mixed models repeated measures analysis. Likewise, to test for differences in longitudinal exposure to CO and NNAL, we will compare the area under the curve over the entire 12 months of follow-up using repeated measures analysis. If the treatment differences are heterogeneous across any covariate sub-groups, we will quantify and report such interactions

with appropriate contrast statements. We will compare the cumulative number of self-reported quit attempts by means of a Wilcoxon rank-sum test.

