#### *Sources of Materials*

This study involves testing alternative methods for reducing the harms of smoking and supporting smoking cessation among smokers with COPD. We will provide participants with standardized information on smoking cessation and the appropriate use of NRT. We will gather data from all of our study participants at baseline and months 3, 6, and 12. Information gathered will include surveys, medical records information, measures of respiratory function, urinary measures of nicotine and cigarette smoke exposure, and measures of expired carbon monoxide (to measure smoke exposure). The baseline questionnaire will collect information related to demographics, smoking history, and health status questions. At baseline, 3, 6, and 12 months, we will collect urine specimens, exhaled CO and will administer a brief survey assessing their current smoking, respiratory symptoms, and history of COPD-related hospitalizations or emergency room visits. In addition, at baseline and Month 12, we will collect a measure of their breathing (i.e., spirometry).

All questionnaires and informed consent documents will be submitted to the KUMC IRB for approval prior to implementation.

The KUMC Department of Preventive Medicine and Public Health has a well-developed structure for data management. Working data is maintained on a single large file server. Inactive files are moved to archival storage under control of an automated system, itself controlled by a DBMS (Ingres) based request system that ensures that all data movement is appropriately logged and commented. The archival storage is hosted on the institutional mainframe computer, which also supports billing and registration. The use of the mainframe ensures several high level support functions for the archive system (e.g., storage in separate fire zones, regular copying of data to new media, and guaranteed availability).

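### Hospital and ED events enter the outcome only through self-report at attended visits, and the protocol describes the event in four different ways

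*Protocol*

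**What the plan says.** **How events are found.** The Measures section tracks respiratory and cardiac events and says of the method: "This will be done by self-report of intercurrent emergency department visits and hospitalizations at each follow-up visit". On timing, the section on study visits says: "Trained research assistants will conduct assessments at baseline and 3, 6, and 12 months post-enrollment". The check that follows is described as: "We will validate both the occurrence and the nature of these self-reported clinical events by blinded physician review of medical records". Table 4 adds a first step by the participant: "Patients will be asked to classify the event as related to their heart or breathing".

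**How the event is described.**
- Table 4 has two rows, respiratory-related and cardiac-related, each covering hospitalizations and ED visits.
- Sources of Materials says that at baseline and months 3, 6 and 12 staff "will administer a brief survey assessing their current smoking, respiratory symptoms, and history of COPD-related hospitalizations or emergency room visits".
- The Analytical Plan, under Specific Aim 1, lists among the dichotomous outcomes the "proportion with 1 or more ED visits or hospitalizations", with no cause given.
- Specific Aim 2 builds a decision tree for COPD-related hospitalization (yes/no), without ED visits or cardiac events.

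**What is already available.** The Study site section describes "an electronic medical record (EMR) with an I2B2 research interface", mentioned there for recruitment.

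**The concern.** The outcome starts from what a participant says at a visit. Someone who does not attend, or does not remember, contributes no event, and nothing later in the described process looks for one. In a COPD population the people most likely to be absent from the final visit include those who were sickest, so the most serious events may be the ones missing.

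The protocol gives weight to these events. It chose COPD partly because differences in clinical outcomes are more likely to be seen there, it says patients want to spend less time in hospital and stakeholders are very interested in clinical events, and it plans a published decision tree for COPD-related hospitalization. With four descriptions of the event, it is also unclear what is collected and what is compared between arms. An analysis plan could settle the definition tested, but it could not restore events that were never collected.

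**Working it through.** **1. Following the described process for each type of participant**

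| Situation | What the process does | Result |
|---|---|---|
| Event reported and real | Blinded review confirms occurrence and nature | Counted |
| Event reported, not real | Blinded review rejects it | Correctly removed |
| Event happened, forgotten | No report, so no review described | Lost |
| Missed month 3 or 6, attends later | May be asked about intervening events | Possibly recovered |
| Misses month 12 | No later study visit | Months 6 to 12 lost: 183/365 days = 50% of follow-up |
| Dies or drops out for good | No later visit | Everything since the last attended visit lost |

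The review can only move the count down. Death is not part of either event row in Table 4.

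**2. The four descriptions side by side**

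| Place | Hospitalizations | ED visits | Cause |
|---|---|---|---|
| Table 4 | Yes | Yes | Respiratory and cardiac, separately |
| Sources of Materials (survey) | Yes | Yes | COPD-related |
| Analytical Plan, Aim 1 | Yes | Yes | Not stated |
| Analytical Plan, Aim 2 | Yes | No | COPD-related |

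If the survey followed the Sources of Materials wording literally, it would not supply the cardiac row of Table 4.

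**3. The plan's own figure**

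The only related sample size is for abstinence: 10% versus 20%, 80% power, 5% type I error (two-sided assumed). With pooled variance and no continuity correction:

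n = [1.96·√(2·0.15·0.85) + 0.8416·√(0.10·0.90 + 0.20·0.80)]² / 0.10² = (0.9897 + 0.4208)² / 0.01 ≈ 199 per arm.

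This matches the stated 199 and does not depend on the event outcome. No power is stated for ED visits or hospitalizations.

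**4. Illustration of what lost events could do**

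The event proportions, risk ratio and capture fractions below are assumptions. Write p for the true control proportion, RR for the risk ratio and s for the fraction of participants with an event who are recorded as such. The observed proportions are a = p·s and b = p·RR·s. With n = 199, d = |a − b| and m = (a + b)/2:

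power = Φ{ [d − 1.96·√(2m(1−m)/n)] / √([a(1−a) + b(1−b)]/n) }.

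For p = 0.30, RR = 0.67, s = 1: a = 0.300, b = 0.201, d = 0.099. Power = Φ[(0.0990 − 1.96·0.04344)/0.04316] = Φ(0.32) = 62.6%.

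For s = 0.8: a = 0.240, b = 0.161, d = 0.079. Power = Φ[(0.0792 − 1.96·0.04013)/0.03993] = Φ(0.01) = 50.5%.

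| Control proportion (RR 0.67) | 100% captured | 90% | 80% | 70% |
|---|---|---|---|---|
| 20% | 42.2% | 38.1% | 34.0% | 29.9% |
| 30% | 62.6% | 56.7% | 50.5% | 44.3% |
| 40% | 80.0% | 73.6% | 66.4% | 58.7% |

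If capture differed between arms and there were no true effect, the observed risk ratio would be the ratio of capture fractions. At 80% and 90% that is 0.90/0.80 = 1.125, or 0.80/0.90 = 0.889 if the arms are swapped. The two-sided rejection rate would be 8.3%, 10.5% and 13.4% for true proportions of 20%, 30% and 40%, against a nominal 5%. The protocol does not show that capture would differ, or in which direction.

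**The case against.** The strongest reply is that much is already in place and that several stronger readings go beyond the text.

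- **Cause.** A reader might infer that the participant decides the cause. Blinded physicians already validate the nature of each reported event; the participant's classification is only a first step.
- **Cardiac events.** A reader might infer that they will not be asked about. Measures and Table 4 plainly intend to capture them, and the Sources of Materials sentence is a summary that does not say it is exhaustive. What stands is a mismatch in wording.
- **All-cause test.** The Aim 1 phrase states no cause and may be shorthand for the Table 4 events. That it tests all-cause use is an inference.
- **Missed visits.** A missed month 3 or 6 visit need not lose its window, since a later visit may pick the event up.
- **Records.** Sources of Materials lists medical record information among the data gathered. It describes no search for unreported events, so the gap stands, but the mention deserves notice.
- **Bias by arm.** LT-NRT has in-person sessions at months 3 and 6 and NRT resupply after the month 3, 6 and 9 sessions, so attendance might differ. But no resupply is tied to month 12, where a missed visit costs most, and payments, reminders and transport help are the same in both arms. Differential loss is possible, not established.
- **DSMB.** A reader might infer that its cardiac counts are incomplete too. Their source is not stated, and side-effect prompts at each contact, a toll-free line and review of serious adverse events form a separate safety route.
- **Fatal admissions.** One could assume 2% to 5% mortality (0.02·199 ≈ 4 to 0.05·199 ≈ 10 deaths per arm) against 30 recorded respiratory admissions per arm, and conclude that 4/30 = 13% to 10/30 = 33% as many again are lost. That is a ceiling. It needs every death to follow an unrecorded respiratory admission in someone with no earlier recorded event, no such rate is in the protocol, and people with under 12 months' life expectancy are excluded.

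What survives is that no route into the event outcome is described for people who die, leave for good, miss the last visit or forget, and that the descriptions disagree.

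**Conclusion.** The concern holds in this limited form. ED visits and hospitalizations enter the event outcome only by self-report at months 3, 6 and 12, and record review is described only for events so reported. Unreported events are not recovered, and the event is described in four ways that must be reconciled.

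The one size that follows from the visit schedule alone is that a missed month 12 visit leaves half of follow-up for events unobserved. The power and rejection rates in the illustration rest on assumed event proportions, risk ratio and capture fractions. They show that moderate loss would matter; they do not estimate the loss. The size and direction of any bias cannot be fixed from the protocol. The primary abstinence outcome and the 199 per arm are unaffected. The point is worth acting on because it concerns data collection, which later analysis cannot repair.

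**What to change.** 1. **Search records for everyone.** At month 12, have staff unaware of treatment arm query the site's electronic record through its research interface for ED visits, admissions and deaths. Cover all consenting randomised participants, whether or not they attended or reported an event.
2. **Use the review already planned.** Send all hits together with all self-reports to the blinded physicians.
3. **Deaths.** Report deaths by arm next to the event outcome. Use a composite including death as a sensitivity analysis only, because putting it in the main outcome would change the endpoint.
4. **One definition.** In Sources of Materials, have the survey ask about any ED visit or hospitalization, including cardiac ones. In Specific Aim 1, test the adjudicated respiratory-related and cardiac-related proportions of Table 4, with all-cause use as supportive. In Specific Aim 2, say how COPD-related hospitalization derives from the adjudicated events.

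The cost is one record query, more records for an existing review, and wording changes. The limit is that care outside the site, for example at the partner health center or other recruiting practices, still depends on self-report. Ascertainment would be better but not complete.

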### Covariates

We will collect a variety of covariates (Table 5). These covariates will allow us to verify the comparability of the two comparison arms at baseline and will also allow us to estimate treatment effects for given personal characteristics (see discussion of CART analysis in the analytic plan). We will assess demographic variables, social history variables that might influence tobacco consumption, smoking related variables, including cpd, nicotine dependence, and biological markers of nicotine consumption, and clinical variables including both objective and subjective assessment of respiratory function and prior history of respiratory-related clinical events.

| Table 5. Co-variate measures |                                                                                                                                                                                  |
|------------------------------|----------------------------------------------------------------------------------------------------------------------------------------------------------------------------------|
| Construct                    | Measure (assessment timepoint)                                                                                                                                                   |
| Demographics                 | gender, age, race, ethnicity, income, education, employment, marital status, family structure (baseline)                                                                         |
| Social history               | Other smokers in the home, presence of home smoking restrictions, anxiety (GAD-2), depression (PHQ-2), health history (baseline)                                                 |
| Smoking Variables            |                                                                                                                                                                                  |
| Smoking history              | Quantity smoked (baseline, Mo 3, 6 & 12), quitting history, use of other tobacco and nicotine products, including e-cigs and NRT, (baseline)                                     |
| Readiness to quit            | Interest in quitting will be assessed using 30 day anchor (stage of change) and 12 months (intent to cut back or quit) (baseline, Mo 3, 6 and 12)                                |
| Nicotine dependence          | Fagerström Test for Nicotine Dependence (FTND) ,  time to first cigarette (baseline, Mo 12); Brief WISDM  among continued smokers at month 12. |
| Nicotine intake              | Urinary cotinine/creatinine ratio (baseline, Mo 3, 6, and 12)                                                                                                                    |
| Clinical Variables           |                                                                                                                                                                                  |
| Respiratory function         | FEV1 (baseline)                                                                                                                                                                  |
| COPD symptoms                | CAT score, # of hospitalizations for COPD in past year (baseline)                                                                                                                |
| Treatment Variables          |                                                                                                                                                                                  |
| Medication adherence         | 3-day medication use recall (Mo 3, 6, and 12)                                                                                                                                    |
| Counseling adherence         | total counseling sessions completed                                                                                                                                              |

